### Time schedule

Recruitment started in June 2013; the target population, 3500–4500 patients, is expected to be accomplished in June 2016. The different centres can start with the study at different times. Each centre will be followed for a period of 1 year and afterwards the data analysis will start.

### Organisation

Each participating centre has provided a contact person who will be in charge of coordinating the study in their centres. The investigators have regular contact with these coordinating people to confirm the fulfilment of the inclusion criteria, the adherence to the study protocol, and to provide support or additional information when necessary.

### Cost analysis

A cost analysis will be performed for both groups (control and intervention).

#### Hospital costs

The analysis will take into account the number of hospitalisations or hospital referrals, consisting of personnel (physician, nurse, pharmacists, etc.), material and equipment costs. These costs will be based on study patients records and standard rates.

#### Costs outside the hospital

This analysis will also take into account the healthcare costs outside the hospital like the addition of new medication.

### Sample size calculation

Calculation of the total number (one event per patient). The aim is to reduce the number of patients with at least one event with 25% by using the CRR compared to the regular care. These events consist of medication related hospital referrals, delirium, falls, and/or deaths.

In order to calculate the sample size a pilot study was performed. Nursing homes physicians from the region (Envida and Zuyderland) have informed, via an electronic questionnaire, about any hospital referrals, delirium and/or falls within their patients. In addition, they stated whether these events could be medication related. This pilot study has lasted for 5 months. No patient information was given.

The pilot study showed a proportion of patients with at least one event (combination of fall, delirium, hospital referral, and death) in the control group of 0.16 and a mean number of patients per physician of 56.

Assuming a proportion of patients with at least 1 event during 1 year follow-up of 0.20 in the control group, a 25% reduction by using the CRR compared to regular care, i.e. proportion reduces from 0.20 to 0.15, and a two-sided significance level (α) of 0.05, the number of patients per group required to detect an effect with 80% power equals 906. Accounting for the design effect (randomisation per physician; DE = 1 + (m-1)*ICC), where we assume an intra-class correlation coefficient (ICC) of 0.01, a mean number of patients per physician (m) of 56 (pilot study), and a 10% dropout rate, the required number of patients increases to 1562 per group.

We assumed a higher proportion of patients with at least one event in the control group (0.20) than the one found in the pilot study (0.16), because the number of falls were underreported in the pilot study and the follow-up duration is now longer, i.e. one year instead of five months.

### Statistical analysis

To account for the cluster randomisation (physicians are randomised, where patients are clustered within physicians), all linear and logistic mixed effects analyses are performed with physicians as random factor.

#### Primary study parameters

To detect a difference in proportions of the primary outcome (composite endpoint consisting of hospital referrals, delirium, falls, and/or deaths) between the groups (control versus intervention), logistic mixed effects analysis are applied with the following fixed factors: group (control or intervention), nursing home organisation (Envida, Zuyderland, Sevagram or Novicare), type of ward (psychogeriatric or somatic) and other variables related to the outcome, like age and sex.

#### Secondary study parameters

For the subgroup analyses (within nursing home organisation or within type of ward), the same analysis method is applied as for the primary outcome variable, excluding the variable that indicates the subgroups.

For the other endpoints, linear or logistic mixed models are used, depending on the type of outcome (numerical or binary, respectively). Furthermore, the same fixed effects as for the primary outcome are included.

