#### Secondary endpoints

As secondary endpoints, the same outcome variable will be used to analyse the possible differences between institutions, to separately analyse psychogeriatric and somatic wards, to analyse the medication related events, and to separately analyse each of the parameters included in the combined endpoint (hospital referrals, delirium, falls, and/or deaths).

In order to get this information, physicians will be asked to report any events including: hospital admission, polyclinic visit, emergency department visit, falls, delirium and death. These questions will be asked via an electronic questionnaire via Google Drive. The assessment of whether the event is or could be drug related or not will be done exclusively by the physician.

The quality of life will be measured using the EQ-5D questionnaire both for patients in the control group and patients in the intervention group. The questionnaire will be performed at the end of the study (i.e. after one year follow-up), both for psychogeriatric and somatic patients. The results will be compared between intervention and control group. For both patients groups a caregiver/nurse will answer the questionnaire.

In addition the analysis of the MAI and the cost evaluation will also be performed for both control and intervention group.

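### The only subgroup method is separate refits of the primary model, which cannot test whether the intervention effect differs between institutions; an interaction term is needed

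*Protocol article*

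**What the plan says.** Three parts of the protocol article bear on this.

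- **Aim.** Under Secondary endpoints: "the same outcome variable will be used to analyse the possible differences between institutions, to separately analyse psychogeriatric and somatic wards". The secondary objectives at the end of the Background describe the institution part differently, as an analysis inside each centre because regular care may vary. They describe the ward part as a separate analysis.
- **Full model.** Under Primary study parameters, a logistic mixed model has fixed factors for group, "nursing home organisation (Envida, Zuyderland, Sevagram or Novicare), type of ward (psychogeriatric or somatic", and covariates such as age and sex. Under Statistical analysis, physician is the random factor. No product of group with organisation or ward is listed.
- **Subgroup method.** Under Secondary study parameters, for analyses within organisation or within ward type, "the same analysis method is applied as for the primary outcome variable, excluding the variable that indicates the subgroups".

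**The concern.** A model fitted to one organisation's data holds no information on the other three. Four such fits give four estimates of the group effect but no contrast between them, and the full model constrains the effect to be the same (on the log-odds scale) in all four. The institution aim, read as a question about where the system works better, therefore has no stated test.

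What is at stake is how the results are read. With separate fits as the only subgroup output, the obvious way to speak of differences is to note which fits are significant and which are not. The trial is sized for the whole sample, so each part is underpowered. Some organisations could then appear to benefit and others not, even though the effect is identical in all. The primary analysis is not affected.

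**Working it through.** **Inputs from Sample size calculation.** "a two-sided significance level (α) of 0.05"; "proportion reduces from 0.20 to 0.15"; "the number of patients per group required to detect an effect with 80% power equals 906"; "we assume an intra-class correlation coefficient (ICC) of 0.01"; 56 patients per physician; 10% dropout; 1562 per group, so 2 × 1562 = 3124 in total. The Population section expects 3500–4500. There are four organisations and two ward types.

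**Step 1: reproduce the plan's figure.** The two-proportion formula with pooled variance and no continuity correction gives 906 per group. The design effect is 1 + (56 − 1) × 0.01 = 1.55. Then 906 × 1.55 = 1404.3, rounded up to 1405, and 1405 / 0.9 = 1561.1, rounded up to 1562. The plan's numbers reproduce.

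**Step 2: effective size per arm** (N/2 × 0.9 / 1.55).
- N = 3124: 1562 × 0.9 / 1.55 = 907. Per organisation 907/4 = 227; per ward 907/2 = 453.
- N = 4500: 2250 × 0.9 / 1.55 = 1306. Per organisation 1306/4 = 327; per ward 1306/2 = 653.

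Equal subgroup sizes are an assumption; the protocol gives none.

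**Step 3: power in each subgroup, 0.20 against 0.15.** Power = Φ[(0.05 − 1.96 × SE_pooled) / SE_unpooled], where SE_pooled = √(2 × 0.175 × 0.825 / n) and SE_unpooled = √((0.20 × 0.80 + 0.15 × 0.85) / n). For n = 227 the SEs are 0.0357 and 0.0356, so power = Φ(−0.56) = 0.288.

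**Step 4: chance of mixed results when the true effect is the same everywhere.** With k independent subgroups, each with power p, this is 1 − p^k − (1 − p)^k.

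| N | Subgroups | Power each | Mixed results |
|---|---|---|---|
| 3124 | 4 organisations | 0.288 | 1 − 0.007 − 0.257 = 0.736 |
| 3124 | 2 wards | 0.509 | 1 − 0.259 − 0.241 = 0.500 |
| 4500 | 4 organisations | 0.390 | 1 − 0.023 − 0.138 = 0.839 |
| 4500 | 2 wards | 0.662 | 1 − 0.439 − 0.114 = 0.447 |

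**Step 5: sensitivity.**
- Unequal organisations (40/30/20/10): 75% at 3124 and 85% at 4500.
- Wards split from 50:50 to 80:20: 50–61% at 3124 and 45–62% at 4500.
- Beta-binomial cluster simulation with equal subgroups (ICC 0.01, 50 patients per physician after dropout, cluster-level t test): 70% (four) and 50% (two) at 3124; 82% and 45% at 4500.
- No effect anywhere: 1 − 0.95^4 − 0.05^4 = 0.185 for four subgroups and 1 − 0.95^2 − 0.05^2 = 0.095 for two.

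A valid interaction test at the 5% level would wrongly declare a difference in 5% of trials.

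**Step 6: power of the interaction test.** Take two equal wards, the full effect in one and none in the other. The log odds ratio is ln(0.15/0.85) − ln(0.20/0.80) = −0.348. The variance of the interaction is the sum over the four ward-by-arm cells of 1/[n p(1 − p)].
- N = 3124 (n = 453): 3/(453 × 0.16) + 1/(453 × 0.1275) = 0.0587, SE 0.242. Power = Φ(0.348/0.242 − 1.96) ≈ 0.30.
- N = 4500 (n = 653): variance 0.0407, SE 0.202. Power ≈ 0.41.

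**The case against.** The strongest reply is that the protocol never says subgroup p-values will be set against each other, nor that significance in one place and not in another will count as a difference. That is correct. A reader might infer that differences are to be judged this way, but the inference is the reader's own; the text only says how the effect is estimated inside each subgroup.

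Second, for wards the method fits the aim. Both the Background and Secondary endpoints promise separate ward analyses and no comparison of the two. Ward is also the randomisation stratum, so a within-ward estimate is a sound secondary analysis. This stands: the mismatch concerns institutions, and a ward interaction is needed only if ward effects are to be compared.

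Third, the institution aim can be read in other ways. The Background wording asks for a within-centre analysis, which the refits deliver. If the aim is about event levels, the organisation main effect in the full model covers it. Both readings are open. Only the third, a difference in the intervention effect, has no test. It is a natural reading, because the endpoint is listed beside the subgroup analyses of the treatment comparison and because varying regular care is a reason for the effect to vary.

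Fourth, a reader might conclude that false disagreement is the usual outcome. That holds only for four organisations under the full planned effect. For two wards it is about a coin toss, and with no effect anywhere it is uncommon.

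Finally, an equal split of 3124/56 ≈ 56 physicians leaves about 14 per organisation, and a 1.96 cut-off on 12 degrees of freedom would have a true error of about 7.4%. One might call this an error in the plan, but the protocol names no cut-off or reference distribution, and that detail commonly belongs in the SAP. It shows that the separate fits are fragile and no more.

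**Conclusion.** The concern holds as a gap between aim and method. The stated analyses estimate the effect within each organisation and ward type, but none tests whether the effect differs between institutions, which is one plain meaning of the secondary aim.

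The misreading risk is conditional. It needs the separate results to be compared informally, the planned effect to be real and the same everywhere, subgroups of roughly the assumed sizes, and each physician to belong to one subgroup so that the fits are independent. Mixed results then occur in about 74% of trials across four organisations and 50% across two wards at 3124 patients, and in 84% and 45% at 4500. With no effect anywhere the figures fall to 18.5% and 9.5%. The documents do not support the stronger statement that the trial will report spurious differences. The point concerns secondary conclusions only and is a low-cost improvement.

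**What to change.** - Add a group-by-organisation interaction to the full primary mixed model, keeping physician as random factor. With four organisations this is a test on 4 − 1 = 3 degrees of freedom. Add a group-by-ward interaction likewise if ward effects are to be compared.
- Report each interaction test with the subgroup estimates and 95% confidence intervals.
- Label the within-organisation and within-ward fits as descriptive, and base any statement that effects differ on the interaction alone.
- Say what is meant by differences between institutions: event levels, within-centre effects, or differing intervention effects.

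The cost is one or two extra model terms and a few sentences, with no new data. The drawback is low power: about 30% at 3124 patients and 41% at 4500 for two equal wards, even when the whole effect lies in one of them. The plan should therefore say that a non-significant interaction is not evidence of equal effects.

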## Discussion

Other studies have mainly focused on surrogate outcomes as primary endpoint. These endpoints, such as reduction of drugs, MAI or drug costs, fail at showing clinical outcomes [10, 12, 15, 26–29]. In the present study, we are focusing both on hard endpoints (i.e. patient relevant outcomes), and surrogate outcomes. The primary endpoint, however, is a combined set of hard endpoints with a clear clinical outcome. For this reason, the duration of this study is one year; other studies not using hard endpoints have shorter study periods [6, 8, 10, 29]. Furthermore, this study is a multicentre study including over 3000 patients making it a relatively large study in comparison with other studies [6, 8, 10, 27, 28].

A major discussion point with other articles is the fact that a great number of studies focus on reducing the amount of prescribed drugs whereas the focus should be on optimising the prescribed drugs (rationalistic pharmacotherapy). This fact enlightens the paradoxically relation between polypharmacy and underprescribing as it might be confronting to add new medication to an already polymedicated patient whereas reducing medication might seem the most logical way to perform [9]. For some patients, optimising the medication will imply reducing the number of drugs, for other patients it will be the changing of some drugs or adding some drugs [30].

We strongly believe that by using a CCDSS, medication reviews are performed in a standardised way which leads to comparable results between patients. In addition, using a CCDSS eliminates the time factor to perform medication reviews as the major problems related to medication, laboratory values, indications and/or established patient characteristics will be directly available. In this way, and in order to make the medication review process complete, consultation within healthcare professionals and/or the patient itself will be time effective and the medication surveillance could be performed around the clock. Especially for polymedicated patients, like nursing home patients, this system provides a hand full of advantages to provide continuous surveillance, improving in this way patient care.

## Abbreviations

CCDSS: (Computerised clinical decision support system)
CRR: (Clinical rule reporter)
ICC: (Intra-class correlation coefficient)
IGZ: (Inspectie voor de gezondheidszorg/dutch health inspectorate)
MAI: (Medication appropriate index)
METC: (Medisch Ethische toetsingscommissie/medical ethical committee)
SCREAM: (Supporting clinical rules engine in the adjustment of medication)
SCREEN: (Supporting clinical rules in the evaluation of elderly patients with neuropsychiatric disorders)
